#### 2.4.4. Randomization and assignment.

Recruitment, randomization, and assignment will be conducted by 4 researchers. Two researchers will be involved in enrolling subjects in the comprehensive care and monitoring of persons with hypertension in primary health care. Another researcher randomized the subjects into 2 parallel groups through block randomization (block size:8) using computer-generated random numbers (random.org). A 4^th^ researcher assigned the participants to 2 groups at an allocation ratio of 1:1. The opaque envelopes enclosing the study group allocation will be numbered consecutively and sealed. Once a patient signs the informed consent form and baseline data acquisition has been concluded, the study researcher will open the envelope with the lowest remaining serial number, and the patient will accordingly be allocated to a group. The subjects will be randomly assigned to 2 groups: a transcendental meditation group and a control group (CG). The CG will remain under pharmacological treatment for 8 weeks and will be set up on a waiting list. Both groups were contacted weekly for adherence and adverse events. The CONSORT flowchart of the participants is shown in Figure 2. A careful explanation of the study’s potential social and academic pertinence and benefits will be provided during the consent action to encourage participant adherence to the intervention and assessments.

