## 2. Material and Methods

### 2.1. Study design and setting

This was a prospective single-center, parallel-group, randomized, controlled trial with concealed allocation and with 8 weeks of follow-up analyzed using an intention-to-treat approach. The study will be performed at the Laboratory of Respiratory Pathophysiology (LAFIR) at the Respiratory Division of the University Hospital (HUMAP) and the comprehensive care and monitoring of persons with hypertension in primary health care. This will be performed according to the SPIRIT (2013) guideline checklist and recommendations. A Schedule of enrollment, interventions, and assessments from the SPIRIT guidelines is shown in Figure 1.

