#### 2.4.5. Blinding.

The 4 researchers involved in recruitment, randomization, and assignment were blinded to the data collection in the lab. In turn, the additional 3 researchers assigned to the lab will be blinded to the randomization and assignment. The subjects and researchers will be strictly advised not to chat or provide clues as to which group they belong. The subjects at the lab will be blinded to the normoxic or hyperoxic gas trials, which will be delivered with similar gas cilinders. The statistician will also be blinded to all the protocols and data collection. Finally, participants were blinded to the study hypotheses.

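### One published block size of 8 at a single centre could let anyone who knows the earlier allocations in a block deduce up to about one in five assignments on average

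*Protocol article*

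**What the plan says.** Section 2.1 describes a "prospective single-center, parallel-group, randomized, controlled trial with concealed allocation". Section 2.4.4 gives the method: the list is produced "through block randomization (block size:8) using computer-generated random numbers (random.org"), "at an allocation ratio of 1:1". No second block size and no stratification factor is mentioned, so the article describes one sequence cut into blocks of four and four.

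The same section sets out safeguards. Tasks are divided: "Two researchers will be involved in enrolling subjects", a third researcher generates the list and a fourth assigns. "The opaque envelopes enclosing the study group allocation will be numbered consecutively and sealed". The next envelope in serial order is opened "Once a patient signs the informed consent form and baseline data acquisition has been concluded".

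On masking, section 2.4.5 states that "The 4 researchers involved in recruitment, randomization, and assignment were blinded to the data collection in the lab". It also masks the three laboratory researchers to assignment, and it tells subjects and researchers not to reveal group membership. It does not say that the enrolling researchers are masked to earlier allocations or to the block size.

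**The concern.** A sealed, numbered envelope stops someone reading the next assignment. It does not stop someone deducing it. Once four of one arm have been used in a block of 8, the rest of that block is fixed. The block size is in print, and the arms are easy to tell apart afterwards because one group attends a meditation course and the other waits. Whoever opens the envelopes sees each arm as it is drawn. Both groups are contacted weekly, and the article does not say by whom, so knowledge of past arms could spread.

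The harm at stake is selection at entry. A person who knows the next arm could hasten, delay or discourage a candidate, and the exclusion criteria in section 2.4.3 leave room for judgement about diseases that interfere with the protocol. With 36 per arm, steered entries could shift motivation, medication adherence or baseline blood pressure between groups. The documents give no basis for putting a size on that shift, and none is claimed here.

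**Working it through.** **Inputs.** Block size 8, ratio 1:1 and a single sequence come from sections 2.1 and 2.4.4. The planned size comes from section 2.4.6: 30 per group, raised by 20% to 36 per group. That step reproduces as 30 × 1.20 = 36, so 72 in total and 72 / 8 = 9 full blocks. The article gives no predictability figure of its own.

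**Certain assignments, fixed block of 8.** The assignments known in advance are the run of identical arms at the end of the block. There are C(8,4) = 70 equally likely blocks:

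| Known in advance | Blocks | Share |
|---|---|---|
| 1 | 40 | 57.1% |
| 2 | 20 | 28.6% |
| 3 | 8 | 11.4% |
| 4 | 2 | 2.9% |

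Mean = (40×1 + 20×2 + 8×3 + 2×4) / 70 = 112 / 70 = 1.6 per block. The general formula with m per arm agrees: 2m/(m+1) = 8/5 = 1.6.

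- Share: 1.6 / 8 = 20%.
- Over the trial: 9 × 1.6 = 14.4 of 72 on average, and never fewer than 9, because the last assignment of each block is always known.
- Same formula for other fixed sizes: block of 4, 1.33 / 4 = 33%; block of 6, 1.5 / 6 = 25%.

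**Condition.** These figures are for an observer who knows the block size and every earlier arm in the current block. For someone who does not know the earlier arms, the number of certain assignments is 0.

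**Best guess, fixed block of 8.** Always guessing the arm that is behind gives 4 + (2^8/70 − 1)/2 = 5.33 correct per 8, or 66.6%, against 50% by chance.

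**Varying block sizes.** This was simulated with 4,000 sequences of 72. Sizes were drawn with equal probability, and the observer knew the set of possible sizes and all past arms but not the current size.

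| Block sizes | Certain assignments | Best-guess accuracy |
|---|---|---|
| 8 fixed | 20.0% | 66.6% |
| 4, 6, 8 | 2.3% | 67.8% |
| 6, 8, 10 | 1.6% | 66.2% |

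With 6, 8 and 10, 0.016 × 72 is about 1.2 certain assignments in place of 14.4. Guessing accuracy hardly moves, and with 4, 6 and 8 it is slightly worse than now. The gain from varying the sizes therefore lies in certainty and not in guessing.

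**The case against.** The strongest reply is that the 20% describes a worst-case observer. Nothing in the article says that the enrolling researchers see, log or are told past allocations. The plan gives enrolment to two people, the list to a third and assignment to a fourth, so those best placed to steer candidates are not given the list or the assigning role. Section 2.4.5 discourages disclosure of group. A condensed article may also leave further masking details to the full protocol. All of this stands, and it is why the point is conditional. Silence about masking to past allocations is not evidence that they are shared.

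The timing of opening also helps. If envelopes are opened only after baseline, a candidate's place in the sequence depends on when baseline is finished, which makes steering at recruitment harder, and baseline values are recorded before the arm is revealed. The Figure 3 caption agrees with this order. Section 2.2, however, places the three initial visits after randomisation, so the article is not consistent on this protection.

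A block of 8 is already less predictable than one of 4 or 6, and the laboratory researchers are masked to assignment. The risk is therefore selection at entry and not biased measurement.

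These replies do not dispose of the point. Whoever opens the envelopes knows the past arms by necessity, and the one other fact needed, the block size, is published.

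**Conclusion.** The point holds as a modest, conditional weakness. With one published block size of 8 at one centre, a person who knows the earlier allocations in a block can deduce up to about 20% of assignments on average, about 14 of 72. A person without that knowledge can deduce none. This assumes a single unstratified sequence, a size of 8 throughout, and 72 participants in complete blocks.

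A reader might infer that the recruiting team does know one assignment in five, or that the claim of a "randomized, controlled trial with concealed allocation" fails. The documents support neither. They do not show that the enrolling researchers have the necessary information, and the division of roles and the sealed envelopes are genuine protection. What they support is that an avoidable opening for selection remains and can be closed at little cost.

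**What to change.** In section 2.4.4:

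1. Generate the unused part of the list with randomly varying block sizes, for example 6, 8 and 10.
2. Withhold the sizes from the enrolling and assigning researchers until the last participant is randomised.
3. State that past allocations are kept from the two enrolling researchers.

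Steps 1 and 2 protect against someone who must see past arms, such as the person opening envelopes: certain assignments fall from 20% to about 2% even if the set of sizes becomes known. Because best-guess accuracy stays near 66% for such a person, step 3 is needed as well. It is the step that protects against guessing by the enrolling pair.

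The cost is regenerating the remaining list and refilling the unopened envelopes. If recruitment stops inside a block, the arms may differ slightly in size, by at most 5 within a block of 10.

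Section 2.2 gives an October 2022 start and an expected 18 months. If randomisation is already complete, the list cannot be changed, and the report should instead state who had access to the block size and to past allocations.

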**Figure 2. F2:**
[figure not shown]
CONSORT 2010 flow diagram for the study.

#### 2.4.5. Blinding.

The 4 researchers involved in recruitment, randomization, and assignment were blinded to the data collection in the lab. In turn, the additional 3 researchers assigned to the lab will be blinded to the randomization and assignment. The subjects and researchers will be strictly advised not to chat or provide clues as to which group they belong. The subjects at the lab will be blinded to the normoxic or hyperoxic gas trials, which will be delivered with similar gas cilinders. The statistician will also be blinded to all the protocols and data collection. Finally, participants were blinded to the study hypotheses.

#### 2.4.6. Sample size.

Since there are no previous studies on CB activity after meditation, our a priori sample size calculation was based on a previously cited pilot study on RCBA ^[47]^. Considering an effect size of 0.25, a minimum of 30 subjects would be necessary to detect a significant change in chemoreception based on within-group analysis. In addition, the sample size was calculated based on a pilot study. The pilot study comprised 12 normotensive/prehypertensive healthy subjects and showed a standard deviation of the mean difference for SBP ± 4.2 mm Hg, during 2 different trial days (see Supplemental Digital Content, http://links.lww.com/MD/I272), with the oscillometric method and under the same experimental conditions (normoxic, see subsection 2.5.7). Based on a repeated measure ANOVA design with 1 between-group factor (Meditators vs Control) and 2 within-groups factors (Gas type and Time), with 4 averaged BP measures [pre-normoxic (T1), pre-hyperoxic (T2), post-normoxic (T3), post-hyperoxic (T4)] for each subject, upon resting condition, 30 subjects per group would be adequate in a 2-sided study to set an error type I = 0.05 and *β* = 0.80. Considering a 20% dropout and exclusion rate, a minimum total sample size of 36 per group was required. This sample size is concordant with several studies on the effects of meditation on hypertension.^[47]^

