#### 2.6.1. Primary outcomes.

The primary outcomes were as follows:(i)BP changes under normoxia.(ii)BP changes under hyperoxia, and.(iii)changes in RCBA after 8 weeks of TM compared with control subjects. Any BP difference for normoxic or hyperoxic trials > ± 5.9 mm Hg, as determined by our reliability study, after 8 weeks will be considered a clinically significant result (Figure S2 and S3, Supplemental Digital Content, http://links.lww.com/MD/I272). To the best of our knowledge, there has been no reproducibility study of the RCBA in adults with hypertension.

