### 2.10. Statistical analysis plan

The 2 groups will initially be compared at baseline in terms of their characteristics, using the chi-squared test for categorical variables and *t*-tests for continuous measures, after Shapiro–Wilk tests for normality. Descriptive analysis will be performed using frequencies and percentages to obtain clinical, anthropometric, and sociodemographic conditions. Two-way ANOVA for repeated measurements will be applied considering between-factors (2 groups) as independent variables and 2 within-factors for BP measurements (gas type and time) as dependent variables (pre-normoxic, pre-hyperoxic, post-normoxic, and post-hyperoxic). A mixed-design with repeated measures will be applied for RCBA, RVV, and EVV as dependent variables in comparing week “0” with week “8.” A post hoc analysis using the Bonferroni procedure, taking into account standard sphericity, will be performed. If this criterion is violated through the Mauchly test, we use the Greenhouse-Geisser correction. In order to explore possible change effects after meditation, coefficients of correlation through Pearson product-moment, including ∆ BP, ∆RVV and ∆ EVV as dependent variables and, ∆RCBA as independent variable, will be performed as percentage of change (∆= (“8 week–“0 week/0 week”)_ *_ 100. Effect sizes (Cohen-d) will also be presented to show the magnitude of our findings, using the scores of 0.20 as small, 0.50 as a medium, and 0.80 as large. Statistical Package for Social Sciences software (version 17.0; IBM Corp, Armonk, NY) was used for all statistical analyses. The study will adopt a *P-value* ≤ 0.05 as statistically significant.

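### The RCBA sample size is justified by a within-group change on an unnamed effect-size scale, but the primary outcome compares TM with control, and no calculation supports that contrast

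*Protocol article*

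**What the plan says.** Section 2.4.6 makes two separate sample-size statements.

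- **RCBA.** From a cited earlier study, with an effect size of 0.25: "a minimum of 30 subjects would be necessary to detect a significant change in chemoreception based on within-group analysis". The text does not say whether 0.25 is Cohen's d, a paired standardised change or Cohen's f. It gives no SD, pre–post correlation, alpha or power for this step, and does not say whether 30 is per group or in total.
- **BP.** From a pilot with an SD of 4.2 mm Hg for the day-to-day difference in systolic pressure: "30 subjects per group would be adequate in a 2-sided study to set an error type I = 0.05", with beta written as 0.80. The design is a repeated-measures ANOVA with group, gas and time. No target difference is named here. On the source of the SD: "The pilot study comprised 12 normotensive/prehypertensive healthy subjects".

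Enrolment is then set at 36 per group to allow for 20% loss.

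Section 2.6.1 lists as primary outcome (iii) "changes in RCBA after 8 weeks of TM compared with control subjects". It also sets a clinically significant BP difference of more than 5.9 mm Hg in either direction, and notes that no reproducibility study of RCBA exists in hypertensive adults. Section 2.10 analyses RCBA in a mixed design comparing week 0 with week 8.

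**The concern.** A before–after change in one group and a difference in change between two groups are different contrasts. With n per arm and equal SDs of change, the standard error of the second is √2 times that of the first. A number adequate for the first is not adequate for the second unless the between-arm effect is correspondingly larger.

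RCBA is the mechanistic primary outcome of a trial that asks what part the carotid body plays in any BP response to meditation. If the between-arm comparison is null, readers will be inclined to conclude that the carotid body is not involved. The stated justification does not show that the trial could detect a relevant difference.

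**Working it through.** **Inputs.** From section 2.4.6: effect size 0.25, n = 30, 36 enrolled per group, 20% loss, BP SD 4.2 mm Hg from 12 people. From section 2.6.1: 5.9 mm Hg. Assumed for RCBA, because the article gives these only for BP: two-sided alpha 0.05 and 80% power. All t-test figures use the noncentral t distribution.

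**1. Can the stated 30 be reproduced?**

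- Paired test, 0.25 as the standardised change (dz): n = 128 for 80% power, and 30 subjects give 26%. This cannot be the source of 30.
- Cohen's f = 0.25, two measurements, correlation ρ: dz = 2f/√(2(1−ρ)). At ρ = 0.5, dz = 0.50 and N = 34 (30 subjects give 75%). At ρ = 0.55, N = 31. At ρ = 0.6, N = 28.

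So 30 is reached only with an added, unstated assumption, such as f = 0.25 with ρ between about 0.55 and 0.6.

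**2. Take 30 as correct within group and carry it to the between-arm contrast.**

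- Paired test, n = 30, 80% power: dz = 0.529.
- Same change in TM, no change in control, equal SD of change, n per arm: noncentrality = 0.529 × √(n/2).

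| Evaluable per arm | Power, TM vs control |
|---|---|
| 30 | 52.2% |
| 29 | 50.8% |
| 28 | 49.4% |

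The rows for 28 and 29 matter because 36 × 0.80 = 28.8. About 58 per arm would be needed for 80%.

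**3. Other readings of 0.25, at 30 per arm, between arms.**

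| Reading | Power |
|---|---|
| d = 0.25 on the change scale | 16% |
| f = 0.25 within group, ρ = 0.5 (dz = 0.50) | 48% |
| f = 0.25 for group × time, ρ = 0.5 | 97% |

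The last reading corresponds to a between-arm difference of 1.0 SD of change, twice the dz of 0.50 that the same f and ρ imply for a within-group change.

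**4. What 30 per arm does detect.** The standardised between-arm difference in change with 80% power is 0.736 (0.75 at 29 per arm, 0.76 at 28).

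**5. BP, against the 5.9 mm Hg threshold, 30 per arm.** The 95% chi-square interval for an SD of 4.2 on 11 degrees of freedom is 3.0 to 7.1. For group × gas × time, if the changes under the two gases are independent, the SD is multiplied by √2.

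| Contrast | SD of change, mm Hg | Power for 5.9 mm Hg |
|---|---|---|
| Group × time, one gas | 4.2 | over 99% |
| Group × time, one gas | 7.1 | about 88% |
| Group × gas × time | 4.2 × √2 = 5.9 | about 97% |
| Group × gas × time | 7.1 × √2 = 10.0 | about 61% |

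**The case against.** The strongest reply is that the text does not fix the RCBA calculation tightly enough to call it underpowered. Alpha and 0.80 belong to the BP sentence. Section 2.4.6 also uses within-groups for the repeated factors of a two-arm model, so the RCBA phrase might refer to the time factor of the mixed design rather than to one arm alone. If 0.25 is f for group × time at ρ = 0.5, 60 subjects in total give 97% power. The cited study and the supplement, neither of which is visible here, may name the scale. The study calls itself exploratory.

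Much of this stands. It rules out any single power figure as fact, and it means that the absence of a correlation from a condensed article is not in itself an error. It does not remove the mismatch. The interaction reading needs 34 in total and so does not yield 30, it sits badly with an analysis described as within-group, and it requires a between-arm effect that the article nowhere states. A range of 16% to 97% across readings shows that the stated input settles nothing for this outcome.

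It is also fair that Cohen's d in section 2.10 is a scale for reporting observed effects. It should not be taken as the sizing scale, particularly as d = 0.25 could not have produced 30.

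**Conclusion.** The point holds in this form: the RCBA justification addresses a within-group change on an unnamed scale, while the primary outcome is a between-arm comparison for which no calculation is given. Power of 80% for RCBA is therefore not shown.

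A reader might infer that the trial has about 50% power for RCBA. The documents do not support that as an unconditional statement. The 52% rests on four assumptions: 80% power at two-sided 0.05 for the RCBA step, no mean change in controls, equal SDs of change, and a between-arm effect equal to the within-group change.

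A reader might also infer that BP power is optimistic, because the SD comes from a few healthy people over two days in normoxia. That does not follow either. Against the article's own 5.9 mm Hg threshold, power is adequate for a single-gas group × time contrast even at the upper limit of the SD. It falls to about 61% only for group × gas × time with the SD at that limit and independent gas changes. What is missing is the link between the calculation and the threshold.

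Writing beta = 0.80 literally means 20% power. It is most likely a slip for power, and is a correction of notation only.

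**What to change.** Revise section 2.4.6 and leave enrolment as it is.

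1. Replace the within-group RCBA statement with the between-arm difference in change that the evaluable sample detects at 80% power: about 0.74 SD of change at 30 per arm, or 0.75–0.76 at 29–28.
2. Name the scale of 0.25 and the pre–post correlation behind it.
3. State that RCBA will be reported as an estimated between-arm difference with a confidence interval, and that a non-significant result will not be read as absence of carotid body involvement.
4. Write power = 0.80 in place of beta = 0.80.
5. Tie the BP calculation to the 5.9 mm Hg threshold of section 2.6.1, with the SD used and its uncertainty, separately for group × time and group × gas × time.

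The cost is a rewritten paragraph and, on the reading that takes 30 as giving 80% within group, a less favourable statement about RCBA. No extra participants are needed, and the planned tests do not change.

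### The 20% attrition allowance was added to 30 per group, not divided out: 36 per group leaves 28.8 evaluable, fewer than the 30 the plan relies on

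*Protocol article*

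**What the plan says.** Section 2.4.6 contains two calculations that both arrive at 30. For resting carotid body activity: "Considering an effect size of 0.25, a minimum of 30 subjects would be necessary to detect a significant change in chemoreception based on within-group analysis". For blood pressure, under a repeated-measures ANOVA with one between-group and two within-group factors: "30 subjects per group would be adequate in a 2-sided study to set an error type I = 0.05", with a power figure of 0.80 that is printed as β. The attrition step comes next: "Considering a 20% dropout and exclusion rate, a minimum total sample size of 36 per group was required". The article gives no formula for that step and no other attrition rate.

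Section 2.4.4 sets 1:1 allocation by "block randomization (block size:8) using computer-generated random numbers". Section 2.1 specifies an intention-to-treat analysis. Section 2.6 says that people who drop out will be encouraged to attend the 8-week assessment. Section 2.4.3 lists among the exclusions non-adherence to the protocol and missing more than two supervised meditation sessions.

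**The concern.** The three printed numbers, 30, 20% and 36, do not agree. If 20% of those randomized are lost, 36 per group does not leave 30 per group. The plan calls 36 a minimum, yet on its own inputs that number falls short of the evaluable size to which the power statement is tied. A reader would take from this section that the trial keeps 80% power with one participant in five lost, and it does not. Someone monitoring recruitment would also stop at 72 believing that a 20% loss was covered.

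**Working it through.** **Inputs, all from section 2.4.6 unless noted**

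- Evaluable number needed: n = 30 per group, taken as stated.
- Dropout and exclusion rate: d = 0.20.
- Stated enrolment: 36 per group, which is 72 in total at 1:1 (section 2.4.4).
- Two-sided α = 0.05; power 0.80 (the printed β is read as power).
- Block size 8 (section 2.4.4).

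**Reproducing the plan's figure**

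- n × (1 + d) = 30 × 1.20 = 36. This matches exactly.
- n / (1 − d) = 30 / 0.80 = 37.5, rounded up to 38. Rounding cannot turn this into 36.

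The allowance was therefore applied as an addition of 20% to the target.

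**What 36 per group delivers**

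- Expected evaluable at 20% loss: 36 × 0.80 = 28.8 per group (57.6 in total, against 60).
- Largest loss that still leaves 30: 1 − 30/36 = 16.7%.
- With 38 per group: 38 × 0.80 = 30.4, which meets the target.
- Shortfall: 38 − 36 = 2 per group, 76 − 72 = 4 in total.

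**Effect on power**

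The article gives no target blood pressure difference or correlation for the ANOVA calculation, so power has to be anchored to its claim that 30 per group gives 80%. Each group-by-time or group-by-gas-by-time interaction in this 2 × 2 × 2 design has one degree of freedom. It is equivalent to a two-sample t-test on a contrast computed for each participant. The standardized difference that gives 80% power at 30 per group is 0.736 with the t distribution. The normal approximation gives (1.960 + 0.842) × √(2/30) = 0.723. Holding that difference fixed:

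| Evaluable per group | Loss from 36 | Power, t-test | Power, normal approximation |
|---|---|---|---|
| 30 | 16.7% | 80.0% | 80.0% |
| 29 | 19.4% | 78.6% | 78.7% |
| 28.8 | 20.0% | 78.3% | 78.4% |
| 28 | 22.2% | 77.1% | 77.2% |

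At the stated 20% loss, power falls by 1.6 to 1.7 percentage points.

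**Chance of keeping 30 (illustration)**

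Assume that each participant is lost independently with probability 0.20. An arm of 36 then keeps at least 30 with probability 0.40, and both arms do so with probability 0.40² = 0.16. For arms of 38 the figures are 0.66 and 0.43.

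**Fit with the blocks**

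72/8 = 9 complete blocks. 76/8 = 9.5, so 38 per group would end part-way through a block. Complete blocks need 80 in total, or 40 per group.

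**The case against.** The arithmetic itself is hard to dispute; the case on the other side concerns its weight.

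- **The gap is small.** It amounts to 1.2 expected participants per group and less than 2 points of power, in a study that describes itself as exploratory. This stands. No design choice turns on it.
- **Real loss may be below 20%.** The analysis is by intention to treat and dropouts will be pursued for outcomes (sections 2.1 and 2.6). This may hold in practice, but it does not repair the calculation. Section 2.4.6 itself budgets 20% as lost, the allowance has no purpose if those participants remain evaluable, and section 2.4.3 lists exclusions that can arise only after a participant has started.
- **The power figures are not the protocol's own.** They rest on a difference solved backwards from the claim of 80% at 30 per group. This stands, and they should be quoted only with that condition. A range of 77–79% for 28 to 29 per group is also slightly too wide for a 20% loss, since 28 of 36 is a 22.2% loss; about 78% is the better single figure.
- **The text calls 30 per group adequate, and 36 a minimum.** Enrolling more is therefore not barred. True, but a minimum that misses its target at the stated loss rate is still wrongly stated.
- **Speaking of a total per group is loose wording only.** Agreed. The context shows that 36 is a per-group number, and nothing here depends on that phrase.

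**Conclusion.** The figure is wrong as written. With 30 evaluable per group and a 20% loss, the required enrolment is 38 per group, not 36; 36 per group tolerates 16.7%. At 20% loss the trial would have about 28.8 per group and about 78% power in place of 80%. The arithmetic uses only numbers printed in section 2.4.6. The power figure also assumes that 30 per group does give 80%, which cannot be checked for blood pressure from what the article reports. This is a modest error that does not threaten the trial, but the stated loss tolerance should be corrected.

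**What to change.** Either of two corrections to section 2.4.6 will do.

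1. **Keep 36 per group (preferred).** State that 72 participants in total, nine complete blocks of 8, preserve 30 per group for losses up to 16.7%. Add that a 20% loss would leave about 29 per group and about 78% power, conditional on 30 per group giving 80%. This costs one sentence and changes no procedure.
2. **Keep the 20% allowance.** Raise the target to 38 per group (76 in total), which means four more participants and a last block left half filled. Filling it takes 40 per group (80 in total), which is eight more than now planned.

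In the same edit, give 36 plainly as the per-group number with 72 as the total, and label 0.80 as power.
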